### Outcome measures

The primary endpoint of the BOOSTB4 trial is safety and tolerability measured as seriousness, severity and frequency of administration-related AEs in the child, fetus and woman after four postnatal or one prenatal and three postnatal intravenous doses of BOOST cells every 4 months. Specific focus will be given to vital signs, transfusion and immune reactions and maternal and fetal AEs using the Maternal and Fetal AE Terminology,^41^ for example, persistent fetal bradycardia following the infusion, tumorigenicity, morbidity and mortality. The trial has clearly defined Stopping criteria on trial, group and subject levels. In case of a serious adverse reaction, the subject may not receive more doses of BOOST cells. The Data and Safety Monitoring Board will review all AEs and adverse reactions.

Vital signs (oxygen saturation, heart rate, respiratory rate, body temperature, blood pressure (only in the pregnant woman), medical examination and signs of suspected pulmonary embolism) are monitored in the child and pregnant woman before, during and until 48 hours (doses 1‒2) or 24 hours (doses 3‒4) after each dose. In the fetus, the following is monitored before, during and until 48 hours after the prenatal dose using ultrasound: fetal heart rate, middle cerebral artery pulsatility index, peak systolic velocity, umbilical artery Doppler pulsatility index and cardiotocography.

The following parameters are analysed in peripheral blood before, and at 1, 24 (doses 1‒4) and 48 hours (doses 1‒2) after each dose (does not apply to the fetus): blood status (haemoglobin, haematocrit, leukocytes, thrombocytes, erythrocytes and mean corpuscular volume), liver (ALAT and ASAT), kidney (Creatinine) and electrolytes (Chloride, Magnesium, Sodium and Potassium). Donor specific antibodies are analysed before the first dose and >3 weeks after each dose.

The secondary endpoints relate to efficacy of four doses of BOOST cells in children with OI. The hypothesis under investigation is that early administration of BOOST cells will ameliorate severe types of OI. The key secondary endpoint is number of fractures from baseline to primary (12 months after the last dose) and long-term (10 years after the first dose) follow-up. Fracture frequency was chosen as the key secondary endpoint because it is the most clinically relevant efficacy variable. Additional secondary endpoints are time to first fracture after each BOOST cell administration, number of fractures at birth in the prenatal group, growth (length/height and weight), change in bone mineral density measured with DXA/DEXA (not a trial specific investigation, optional and according to the national follow-up programme), clinical OI status and biochemical bone turnover in peripheral blood. The analysis of biochemical bone turnover includes Calcium, Phosphate, Albumin, Parathyroid hormone, 25-OH Vitamin D, Alkaline phosphatase, Bone-specific Alkaline phosphatase, Osteocalcin and cross-linked C-telopeptide of type I collagen, and will be carried out before each dose and then according to the clinical routine every 6‒12 months. No radiological measurements will be performed specifically for the trial.

The exploratory endpoints investigated by the trial include assessing the impact of the therapy on Quality of Life using the Infant Toddler Quality of Life Questionnaire (ITQOL), collection of peripheral blood before and at 1 and 24 hours (doses 1‒4) and 48 hours (doses 1‒2) after each dose for studying the paracrine effect (via the Olink technology or ELISA) and the effect on endogenous immune cells (via flow cytometry) of BOOST cells in subjects and prospective controls (blood sampling optional). The extent of donor cell engraftment in tissue samples collected from routine surgery will be studied, and a method for non-invasive method for prenatal diagnosis of OI developed (not used as the diagnostic method in the trial). In addition, there will be a substudy to BOOSTB4, where parents will have the option to take part in two semistructured interviews, in which their experiences of their participation in the trial are explored. This will allow us to understand their reasoning for their child to participate in the trial, and what has been positive and what can be improved in future similar studies.

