### Blinding, intervention and follow-up

It would not be ethically appropriate to perform a randomised double-blind placebo-control trial in this population, particularly regarding the risks of the prenatal infusion procedure and the vulnerability of the subjects. No blinding or randomisation will therefore take place.

Four intravenous doses of BOOST cells are administered at 4 month intervals (range 3–5 months), please see figure 1 for an overview of the trial. For postnatal subjects, the first dose must be administered before 18 months of age (in the original protocol, it was before 12 months of age; an amendment that has been approved by the Competent Authorities). For prenatal subjects, the first dose will be given in utero during gestational weeks+days 16+0–35+6 via ultrasound-guided injection into the umbilical vein within the fetal liver, and the final three doses are administered postnatally. Each dose contains 3×10^6^ allogeneic expanded human fetal liver MSCs per kg bodyweight. All doses to a subject will be derived from one donor. No preconditioning or medicines after the administration will be administered.

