**Figure 1 F1:**
[figure not shown]
Overview of the trial schedule. The BOOSTB4 trial consists of two parts; part 1 that includes information, consent, screening and inclusion. This is followed by four doses of BOOST cells at 4±1 month intervals with immediate in-patient follow-up over 48 hours after doses 1‒2, and over 24 hours after doses 3‒4 (48 hours for doses 1‒3 in the prenatal group). Part 1 of the trial also includes the primary follow-up at 6 and 12 months after the fourth and last dose. Part 2 of the trial consists of yearly long-term follow-up over 8 years until 10 years after the first dose. BOOST, Boost Brittle Bones Before Birth.

In-patient follow-up is performed over 48 (doses 1–2) or 24 (doses 3–4) hours in the postnatal group and over 48 (doses 1–3) or 24 (dose 4) hours in the prenatal group after each dose. Primary follow-up is performed at 6 and 12 months after the last dose, and long-term follow-up is performed yearly until 10 years after the first dose. At each visit and follow-up, AEs and parameters related to efficacy outcomes are recorded. Women in the prenatal group are followed under the same schedule.

Prospective controls will be subject to the same follow-up routine as the patients enrolled in the treatment group, as described above, with the option to opt in or out from blood collection. The clinical evaluation programme for the historical control group will be based on data available from the routine follow-up of OI patients in the respective country. The controls will be individually matched to each subject (see table 2). Between one and five historical controls will be included per subject and up to 30 prospective controls in total.

**Table 2 T2:** Matching of the controls

Matching of the controls	
The controls historical and untreated prospective will be individually matched to each trial subject:	
Type of OI*:	Type 3 with type 3. Severe type 4 with severe type 4.
Age at onset of bisphosphonate therapy:	Start of bisphosphonate treatment in the first 2 months of life. Start of bisphosphonate treatment from 2 to 12 months of life.
If possible (if more than five controls have been identified), matching will also be made on:	
Sex	
Identical OI pathogenic sequence variant	
Time for OI diagnosis	A control matched with a subject in the postnatal group was diagnosed† postnatally. A control matched with a subject in the prenatal group was diagnosed† prenatally.

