### Statistical analysis

The primary endpoint of the BOOSTB4 trial is the safety of postnatal or prenatal and postnatal administration of BOOST cells. It involves investigation of the seriousness, severity and frequency of treatment-related AEs in the child, woman and fetus. All reported AEs (regardless of the cause) will be included in the statistical analysis, and all analyses will be performed separately for the infant/child, fetus and pregnant woman. No imputation of missing data will take place.

The BOOSTB4 trial is a non-randomised trial and specific caution will be taken to control for problems with bias. The statistical analysis will include descriptive statistics of the data that will be discussed in relation to the general knowledge of the condition, to generate an overall picture of the safety and efficacy profile of the treatment. All trial subjects will be compared with himself or herself as his or her own control over time (longitudinally from baseline to the primary follow-up at 12 months after the last dose and to the long-term follow-up until 10 years after the first dose). In the analysis of parameters such as blood status and biochemical bone turnover, non-parametric Wilcoxon matched pairs signed-rank test (before vs after doses and over time) will be used. One to five matched historical controls (18–90 in total) will, as far as possible, be included per trial subject to increase the statistical precision, and up to 30 prospective untreated controls will also be included.

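### The primary-window fracture endpoint is worded as a count whose observation time depends on dose timing (21–27 months with four doses), with no rule for incomplete dosing and no stated index date for controls

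*Protocol article*

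**What the plan says.** All references are to the protocol article.

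- **Outcome measures**, on the endpoint: "The key secondary endpoint is number of fractures from baseline to primary (12 months after the last dose". The same sentence adds a second window: "and long-term (10 years after the first dose) follow-up".
- The next sentence gives the reason for the choice: "Fracture frequency was chosen as the key secondary endpoint because it is the most clinically relevant efficacy variable". It speaks of frequency but gives no time denominator.
- **Blinding, intervention and follow-up**, on dosing: "Four intravenous doses of BOOST cells are administered at 4 month intervals (range 3–5 months".
- **Figure 1 legend**, on what the follow-up is tied to: "primary follow-up at 6 and 12 months after the fourth and last dose". The legend also says that Part 2 lasts 8 years and ends 10 years after the first dose.
- **Outcome measures**, on early end of dosing: "In case of a serious adverse reaction, the subject may not receive more doses of BOOST cells".
- **Controls** (Blinding, intervention and follow-up; Table 2): prospective controls follow the same follow-up routine as treated children. Data on historical controls come from routine care. The matching table covers OI type and age at start of bisphosphonates, then sex, sequence variant and time of diagnosis where possible. It sets no index date and no length of observation.

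**The concern.** A count of events means little without the time over which it was collected. Here the end of the primary window is set by the date of the last dose, so three things follow from the wording.

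1. Children who receive all four doses within the permitted intervals are still observed for different lengths of time.
2. A child who stops dosing either has a shorter window or has none, depending on what the last dose means. In the first case, a course stopped for a serious adverse reaction would tend to show fewer fractures simply because less time was counted.
3. Historical controls have no dose from which to measure, so a treated child's count and a matched control's count need not cover comparable time.

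This matters because the protocol itself calls fracture frequency the most clinically relevant efficacy variable, and the comparison with controls is not randomised.

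**Working it through.** **Inputs.** Four doses, hence three intervals; interval 4 months, permitted range 3–5 (Blinding, intervention and follow-up). Follow-up after the last dose: 12 months (Outcome measures). Assumption: baseline is the first dose.

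**The plan's own figure.** Part 1 lasts 10 − 8 = 2 years = 24 months (Figure 1 legend). The formula, window = (doses − 1) × interval + 12, gives 3 × 4 + 12 = 24 months. The two agree.

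**Permitted range with four doses.**
- Shortest: 3 × 3 + 12 = 21 months, which is 21/24 − 1 = −12.5%.
- Longest: 3 × 5 + 12 = 27 months, which is 27/24 − 1 = +12.5%.
- Longest over shortest: 27/21 = 1.29.

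**Early end of dosing, if the last dose is the last received.**

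| Doses given | Window at 3 / 4 / 5 months | At 4 months, relative to 24 |
|---|---|---|
| 1 | 12 / 12 / 12 | −50% |
| 2 | 15 / 16 / 17 | −33% |
| 3 | 18 / 20 / 22 | −17% |

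If the last dose is the fourth, as the Figure 1 legend reads, none of these children has a defined window.

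**Effect on counts with no treatment effect.** Expected count = annual rate × months / 12. The rate is an assumption. The Introduction gives 2 per year for one earlier patient, before booster doses between 8 and 13 years of age, which is much older than the children here. Hence a range is shown.

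| Rate per year | 12 months | 21 months | 24 months | 27 months |
|---|---|---|---|---|
| 1 | 1.0 | 1.75 | 2.0 | 2.25 |
| 2 | 2.0 | 3.5 | 4.0 | 4.5 |
| 4 | 4.0 | 7.0 | 8.0 | 9.0 |

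The ratios do not depend on the rate chosen.

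**Effect on a group mean.** If one of 15 postnatal children stopped after dose 1 and the rest had 24 months, mean observation would be (14 × 24 + 12)/15 = 23.2 months, or −3.3%. With two such children it would be (13 × 24 + 2 × 12)/15 = 22.4 months, or −6.7%. In a group of three, one such child gives (2 × 24 + 12)/3 = 20 months, or −16.7%.

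**Historical controls.** At equal rates, a control observed for T months has T/24 of the expected count of a child observed for 24 months. A 12-month record, for example, gives 0.50. The article states no T, so the size here cannot be bounded from the text.

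**Long-term window.** Its end is 10 years after the first dose, whatever the intervals or number of doses. Only death or dropout shortens it.

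**The case against.** The strongest reply is that this article condenses a fuller protocol, that an analysis plan may exist, and that the word frequency suggests a rate. Person-time and the handling of early stopping are often settled in such a plan. This has weight: the wording does not prove that raw counts will be compared. But the article itself fixes the endpoint as a number over a stated window, and the end of that window is the source of the problem.

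A reader might infer more than the text supports:

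- *That controls have no window at all.* This is too strong for prospective controls, who follow the treated children's routine. For them only the starting date is missing.
- *That the window certainly shrinks when dosing stops.* This follows only if the last dose means the last received; the Figure 1 legend points to the fourth.
- *That the whole endpoint is affected.* The 10-year window is not tied to the last dose.
- *That time to first fracture counts one event several times.* The plan does list it ("Additional secondary endpoints are time to first fracture after each BOOST cell administration"), but repeated counting depends on whether time is cut at the next dose, a rule that can properly stand in an analysis plan.
- *That missing observation time will be ignored.* The sentence "No imputation of missing data will take place" stands in the paragraph on the primary safety endpoint and does not settle how fracture time is handled.

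It is also fair to say that the spread among children with four doses is moderate, that it has no evident direction, that no early stop is reported, and that deaths and administration-related events are reported under the primary endpoint. The analysis is descriptive, with no formal power calculation. These points lower the severity; they do not remove the unequal observation time.

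**Conclusion.** The concern holds in limited form. As worded, the primary-window count covers 21 to 27 months in children who receive four doses, so counts can differ by up to a factor of 1.29 at the same fracture rate. The figure assumes that baseline is the first dose, and it sets all three intervals at opposite extremes. For a child who stops early, the nominal window is 12, 16 or 20 months on one reading and undefined on the other; the Figure 1 legend and Outcome measures must be reconciled on this. Historical controls lack a stated window, and prospective controls lack a stated anchor date. The long-term window is sound as to dose timing, although death or dropout still shortens a raw count there. The plan should be corrected, but since the trial is exploratory and its analysis descriptive, the defect is not critical. The text does not show that any actual result is biased.

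**What to change.** Define the key secondary endpoint as fractures per person-year, with actual observation time as the denominator, over a fixed window from the first dose, for example 24 months.

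- **Prenatal subjects:** start the clock at birth, so that time in utero is not counted, and report fractures at birth separately, as already planned.
- **Controls:** apply the same window, from a matched-age index date, to historical and prospective controls alike, and state the observation time available for each.
- **Incomplete follow-up:** keep children who stop dosing in the analysis for their full observed time, and report deaths alongside the rate in both the primary and the 10-year window.
- **Wording:** reconcile the Figure 1 legend with Outcome measures on what the last dose means when fewer than four are given, and number of fractures with fracture frequency.

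The choice of count model and the censoring rule for time to first fracture can be left to the analysis plan.

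The cost is small. Treated children need no new measurements, since time to first fracture already calls for fracture dates. For historical controls, the dates covered by the record must be extracted. The end of the fixed window will not coincide exactly with the visit 12 months after the last dose: with four doses that visit falls between 3 months before and 3 months after month 24, and for prenatal subjects the gap also depends on the time from first dose to birth. Because the article describes open-label primary follow-up as under way, the change should be dated and documented, and the count as now worded can be reported next to the rate.

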### Statistical analysis

The primary endpoint of the BOOSTB4 trial is the safety of postnatal or prenatal and postnatal administration of BOOST cells. It involves investigation of the seriousness, severity and frequency of treatment-related AEs in the child, woman and fetus. All reported AEs (regardless of the cause) will be included in the statistical analysis, and all analyses will be performed separately for the infant/child, fetus and pregnant woman. No imputation of missing data will take place.

The BOOSTB4 trial is a non-randomised trial and specific caution will be taken to control for problems with bias. The statistical analysis will include descriptive statistics of the data that will be discussed in relation to the general knowledge of the condition, to generate an overall picture of the safety and efficacy profile of the treatment. All trial subjects will be compared with himself or herself as his or her own control over time (longitudinally from baseline to the primary follow-up at 12 months after the last dose and to the long-term follow-up until 10 years after the first dose). In the analysis of parameters such as blood status and biochemical bone turnover, non-parametric Wilcoxon matched pairs signed-rank test (before vs after doses and over time) will be used. One to five matched historical controls (18–90 in total) will, as far as possible, be included per trial subject to increase the statistical precision, and up to 30 prospective untreated controls will also be included.

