## Methods and analysis

### Trial design

Boost Brittle Bones Before Birth (BOOSTB4) is an exploratory, open-label, multicentre, phase I/II trial evaluating safety and efficacy of four postnatal intravenous doses (n=15 infants) or one prenatal and three postnatal intravenous doses (n=3 fetuses in the amended protocol, in the original protocol it was n=15 fetuses) of allogeneic expanded fetal MSCs (BOOST cells) for the treatment of severe OI compared with a combination of historical (1–5/subject) and up to 30 untreated prospective controls. Please see the trial synopsis in online supplemental material.

10.1136/bmjopen-2023-079767.supp1Supplementary data

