### Eligibility and recruitment

The inclusion and exclusion criteria for the three trial groups are described in table 1. The upper age limit was amended from maximum 12 months of age to 18 months of age in the postnatal group. This change to the original protocol has been approved by the Competent Authorities, and was implemented to allow for inclusion of more subjects to the postnatal group. All subjects (the postnatal, prenatal and control groups) will receive bisphosphonate treatment. At least one dose of bisphosphonate must be administered before the first dose of stem cells in the postnatal group. In the prenatal group, the first dose of bisphosphonates will be administered after birth. Acceptable types of concomitant medication including bisphosphates during the trial and until the 12 month follow-up are pamidronate (preferred) or neridronate, and the annual dose of bisphosphate is 8‒12 mg/kg body weight per year.

**Table 1 T1:** Inclusion and exclusion criteria for subjects in the BOOSTB4 trial

Inclusion criteria		
**Postnatal group (n=15**)*†	**Prenatal group (n=3**)*‡§	**Control group (n=18–120**)*

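### Statistical analysis compares each child with itself, which cannot separate a cell effect from age, growth and bisphosphonate, while Trial design promises a comparison with controls

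*Protocol article*

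**What the plan says.** In the protocol article, Statistical analysis states that "All trial subjects will be compared with himself or herself as his or her own control over time". The window runs "longitudinally from baseline to the primary follow-up at 12 months after the last dose", and then to ten years after the first dose. The section adds a paired Wilcoxon signed-rank test, before against after dosing and over time, for laboratory parameters including biochemical bone turnover, which Outcome measures lists as a secondary efficacy endpoint. On controls, it says that matched historical ones are to "be included per trial subject to increase the statistical precision, and up to 30 prospective untreated controls will also be included". It writes down no treated-versus-control contrast.

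Trial design describes the evaluation of safety and efficacy differently: the cells are studied "for the treatment of severe OI compared with a combination of historical (1–5/subject) and up to 30 untreated prospective controls". The Abstract says the same.

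Eligibility and recruitment states: "All subjects (the postnatal, prenatal and control groups) will receive bisphosphonate treatment". It also states: "At least one dose of bisphosphonate must be administered before the first dose of stem cells in the postnatal group". No minimum time between the two is given. In the prenatal group bisphosphonate starts after birth, so after the first cell dose. Table 2 matches controls to subjects on OI type and on age band at bisphosphonate start.

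Under Outcome measures, the key secondary endpoint is the number of fractures counted from baseline onward. Growth is listed as length or height and weight.

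**The concern.** Age, growth and bisphosphonate exposure all change over the same months as cell exposure. A comparison of a child with its own earlier state attributes the sum of these changes to the cells. Only children who did not receive cells, observed over the same ages and on the same background treatment, can show how much of the change would have happened anyway. That is the main job of controls in a non-randomised trial; precision is a by-product. The article plans and matches such controls, but the section that governs the analysis does not use them for this purpose.

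Outcome measures states an efficacy hypothesis, and the strengths and limitations list says that a positive result may lead to a pivotal trial. A reading of efficacy that could arise from inactive cells would be a poor basis for that step, and a false impression of harm could wrongly end the programme.

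**Working it through.** **1. The plan's own figures.** With 15 + 3 = 18 subjects and 1 to 5 historical controls each, historical controls number 18 × 1 = 18 to 18 × 5 = 90, as Statistical analysis states. Adding 0 to 30 prospective controls gives 18 to 120, as Table 1 states. The comparator is therefore planned.

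**2. Length of the within-child window.** Four doses have three intervals of 3 to 5 months, and primary follow-up is 12 months after the last dose:
- shortest: 3 × 3 + 12 = 21 months
- nominal: 3 × 4 + 12 = 24 months
- longest: 3 × 5 + 12 = 27 months

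For a postnatal child whose first dose is before 18 months of age, the window is longer than the life lived before it.

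**3. What each endpoint can show within a child.**
- Length and weight: absolute values rise in any growing infant, with or without cells.
- Fractures: the endpoint is a count from baseline onward, so a self-comparison needs either an earlier rate from a short period in infancy or a split of follow-up into earlier and later parts. Both are confounded with age. Prenatal subjects are first dosed in utero and have no usable pre-dose fracture rate.
- Bone turnover: the Introduction says bisphosphonates reduce bone resorption, so turnover markers could shift for that reason alone.

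**4. Algebra for the fracture rate.** Let C be the rate ratio due to cells and B the background ratio due to age and bisphosphonate.
- Own-control ratio = C × B. With inactive cells C = 1, so the result is B.
- Treated against control = (C × B in treated) / (B in controls) = C, if the drift is shared.

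For example, B = 0.5 with inactive cells reads as a 50% reduction, and B = 1.25 reads as a 25% rise.

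**5. Illustrative simulation, cells inactive.** The article gives no fracture rates, so every input here is assumed: gamma-Poisson counts, a pre-dose rate of 2 or 4 fractures per year, between-child coefficient of variation 0.7, 0.75 years before and 2 years after baseline, and 3,000 runs per setting. The test is a two-sided 5% Wilcoxon signed-rank test, on the child's own change or on that change minus the change in one matched control with the same drift. The table uses n = 15, the postnatal group; each range covers the two pre-dose rates.

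| Background ratio B | Own control: false benefit | Own control: false harm | Against one control: false benefit |
|---|---|---|---|
| 1.0 | 1.4–1.7% | 3.7% | 2.4–3.1% |
| 0.8 | 7.4–14.5% | 0.2–0.4% | 2.5–2.6% |
| 0.6 | 25.9–53.8% | 0.0–0.1% | 2.0–2.7% |
| 0.5 | 45.4–73.8% | 0.0% | 2.3–2.5% |
| 0.4 | 61.9–90.4% | 0.0% | 2.3% |
| 1.25 | 0.0–0.2% | 17.7–25.2% | 1.7–2.4% |
| 1.5 | 0.0% | 42.9–64.9% | 2.2–2.4% |

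The nominal one-sided error is 2.5%. With n = 18, false benefit is 8.5% to 94.2% for B from 0.8 to 0.4, and false harm is 20.6% to 73.9% for B of 1.25 and 1.5.

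**The case against.** The strongest reply is that the article already plans the right comparison. The Abstract and Trial design state it, all groups receive bisphosphonate, Table 2 matches on its start, historical controls must have fracture and growth data, and prospective controls follow the same visit routine. The precision phrase may only explain why up to five controls are sought per subject. Statistical analysis speaks of descriptive statistics and caution about bias, names no test for fractures or growth, and serves an exploratory trial whose primary endpoint is safety. Effect measures such as rate ratios and z-scores may be in an SAP that is not shown.

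Most of this stands as fact. A reader might infer that self-comparison is the only efficacy comparison in the article; it is not. The reply does not remove the disagreement between sections, however. Statistical analysis fixes the own-control comparison, applies a paired test to an efficacy endpoint, and states no control contrast. Descriptive before-and-after summaries carry the same confounding, and caution about bias is not a comparator.

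Two stronger readings are tempting and unsupported:
- A reader might infer that the own-control analysis would show benefit on fractures. The article gives no natural-history rate. Its Introduction reports that meta-analyses of randomised trials did not demonstrate fewer fractures on bisphosphonate, although individual studies did. The bias reverses if fractures become more frequent with age.
- A reader might compute a pre-dose rate from birth, counting fractures present at birth, and obtain a large artificial reduction. The article defines no such rate. It lists fractures at birth as an endpoint for the prenatal group only, where they come after the first dose.

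**Conclusion.** The point holds as an internal inconsistency with a real analytic consequence. Statistical analysis does not carry through the comparison with controls that the Abstract and Trial design promise, and the comparison it does name cannot isolate a cell effect. For fractures the error could run either way. For absolute length and weight, a rise is certain in growing infants and says nothing about the cells.

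The simulated percentages illustrate the possible size and are not predictions. They depend on the assumed rates, spread and windows, and on a significance test for fractures that the article does not specify. The 2% to 3% for the control contrast assumes that the control shares the child's drift exactly. Historical controls followed by national routine may not, so some bias can remain after the change.

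**What to change.** In Statistical analysis, bring the text into line with the Abstract and Trial design:
- State that efficacy statements rest on treated against matched control over the same age interval, each control taking its interval from its matched subject. Use a fracture rate ratio, the change in age- and sex-standardised length and weight z-scores, and bone turnover against prospective controls where blood was sampled. The rate ratio needs no pre-dose rate, so it can also be reported for prenatal subjects.
- Present own-control series and paired tests as descriptive only, with no efficacy conclusion drawn from them.
- State that the controls serve to separate the cell effect from age and bisphosphonate, as well as to add precision.

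The cost is wording in the protocol and SAP; the controls and their data are already planned. The efficacy result may look less favourable and will be less precise, because control variability enters the estimate and blood sampling in prospective controls is optional.
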